### Additional consent provisions for collection and use of participant data and biological specimens {26b}

Not applicable, all data which will be collected from the participant is outlined in the informed consent and would only be used to address the topics listed among the objectives of this study. Moreover, this trial does not involve collecting biological specimens for storage.

## Interventions

### Explanation for the choice of comparators {6b}

In this study, we have chosen to use a control group as a comparator. The control group is made up of individuals who are also patients hospitalized in the ICU and receive the same standard ICU care to address their health needs as participants in the intervention group, only without the VR stimulation.

### Intervention description {11a}

The intervention for this study consists of relaxing VR stimulation, which will be started as soon as possible after obtaining informed consent. As stimulation material, immersive 360-degree videos (e.g. nature environments, animals, urban parks) will be played inside a commercially available head-mounted display, with the video sound played inside noise-cancelling headphones. A single video will be shown during each stimulation period, with each video lasting 30 min in length; however, the length may be shortened based on individual participant reaction. The stimulation will be provided three times per day, morning, midday, and evening, every day until the patient is discharged from the ICU, or the maximum of 14 days has been reached. A new video will be played during each stimulation. A total of 44 videos were filmed. All videos shown on the same day will depict the same location, but at different time points. The location shown on a given day is randomly assigned. Videos filmed in the morning, midday, or evening will be shown in the morning, midday, or evening, respectively.

The intervention group will also receive standard ICU care and, if needed, receive treatment for delirium (local delirium protocol), same as in the control group. Therapy would include pharmacological agents (e.g. quetiapin) and non-pharmacological interventions (e.g. early mobilization, communication tools, sleep improvement, family involvement). The first 100 participants, regardless of their group, will additionally be equipped so data can be recorded regarding movement patterns.

### Criteria for discontinuing or modifying allocated interventions {11b}

Participants will be withdrawn from the study if they voluntarily withdraw informed consent at any time. Moreover, participation in the study will be discontinued if:
There are changes in their health status that makes continued participation inadvisableThere are safety concerns

The target length of the intervention is 30 min, but stimulation can be stopped prior to achieving this goal per participant request, or perceived negative reaction of the participant, regardless of the discontinuation criteria listed above.

### Strategies to improve adherence to interventions {11c}

VR stimulation will be provided to the participants by trained ICU nurses who are part of the study team; therefore, adherence while in the ICU should be very high. To ensure adherence at 6 months post-ICU discharge, the participants will be contacted by a member of the study team. The follow-up visit would also take place during a standard patient follow-up appointment.

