Other pre-specified outcome variables include physiological parameters, feasibility of using the VR stimulation by ICU nurses, cognition at ICU discharge and 6 months post-discharge, health-related quality of life and functional independence before ICU admission and 6 months post-discharge, disease-related data, and survival 6 months post-discharge from the ICU. Physiological parameters (e.g. blood pressure, heart rate, respiration rate) will be recorded continuously and changes from baseline, or the start of an event such as VR stimulation, will be compared to later time points. The changes occurring in these parameters over time, together with disease-related data, are of interest and could indicate what effect, if any, VR stimulation has on the condition of the participant. Scores for health-related quality of life, functional independence, and clinical frailty before ICU admission and 6 months post-discharge, and cognition before ICU discharge and 6 months post-discharge, will be compared to determine if any significant differences occur. Additionally, the average survival 6 months post-ICU discharge will be compared between groups. Looking at these variables between groups is important as cognition, health-related quality of life, independence, frailty, and mortality, among others, are known to be negatively impacted by the presence of delirium during the time spent in the ICU. Therefore, it is meaningful to identify if there were any significant changes in these aspects for individuals in the treatment group compared to the controls. It will also be important to determine if providing such an intervention is feasible for the care providers. For this, the validated System Usability Scale will be completed by the nurses in order to understand if overall, the use of this technology was accepted and whether or not it could be integrated into standard ICU care practices [29].

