## Assignment of interventions: blinding

### Who will be blinded {17a}

The research team will not be blinded after assignment to interventions, nor will any member of the interprofessional team be blinded when carrying out the intervention. However, an independent statistician who will be conducting the interim analysis will be blinded.

Additionally, the analysis of the primary outcome of incidence of delirium, and secondary outcome looking at the duration of delirium, will be done blinded.

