### Procedure for unblinding if needed {17b}

Only one person, the independent statistician, is blinded during the intervention period of this study. If required, unblinding could occur after the interim analysis has been conducted.

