Cognitive impairment will be assessed by the study team before ICU discharge and 6 months post-discharge using the Montreal Cognitive Assessment [45]. The Montreal Cognitive Assessment has a known reliability of *κ* = 0.83 [45] and an established content validity in English and in French [45] and a sensitivity of at least 0.90 [46]. The average survival 6 months post-discharge will be obtained via a central database.

The study ends with a follow-up assessment 6 months after admission to the ICU. The study team interviews the participants during a regular follow-up session at the ICU. During the interview, the EQ-5D-5L, Functional Independence Measure, Clinical Frailty Score, and Montreal Cognitive Assessment will be administered. All assessments will be conducted according to the standard ICU care by trained ICU nurses.

In a final step following the VR intervention, the ICU nurse responsible for the intervention will be asked about the feasibility of applying the intervention, completing the 10-item System Usability Scale [29]. The System Usability Scale has a strong reliability score *κ* > 0.89 [47, 48] and an established construct validity, as well as concurrent validity (*r* = 0.86) [47, 48].

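### The unblinded study team takes the 6-month cognition, function and frailty scores, so rater expectation can bias these lower-tier comparisons, chiefly the MoCA

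*Protocol article*

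**What the plan says.** All references are to the protocol article.

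- **Who rates at 6 months.** Plans for assessment and collection of outcomes {18a}: "The study team interviews the participants during a regular follow-up session at the ICU". It continues: "During the interview, the EQ-5D-5L, Functional Independence Measure, Clinical Frailty Score, and Montreal Cognitive Assessment will be administered". On cognition it says "Cognitive impairment will be assessed by the study team before ICU discharge and 6 months post-discharge using the Montreal Cognitive Assessment". The same section assigns the assessments to trained ICU nurses.
- **Who is blinded.** Who will be blinded {17a}: "The research team will not be blinded after assignment to interventions". Sequence generation {16a} also says that the team is not blinded. The only masking in {17a} is for the interim statistician and for two analyses: "the analysis of the primary outcome of incidence of delirium, and secondary outcome looking at the duration of delirium, will be done blinded". On breaking the blind, section {17b} adds: "Only one person, the independent statistician, is blinded during the intervention period of this study".
- **Overlap of roles.** Strategies to improve adherence {11c} places the nurses who give VR within the study team. Implementation {16c} has the study team enrol participants.
- **Use of the scores.** Outcomes {12} compares them between arms: "it is meaningful to identify if there were any significant changes in these aspects for individuals in the treatment group compared to the controls".

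The sentence in {11c} on 6-month contact, "To ensure adherence at 6 months post-ICU discharge, the participants will be contacted by a member of the study team", concerns attendance. It does not say who does the rating.

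**The concern.** In the ICU the headset makes it hard to hide the arm from staff. That reason is gone at 6 months. Under {18a}, VR stops at ICU discharge and no later than day 14 after admission, and the article describes no task at the 6-month visit for which the allocation is needed. Yet the team that knows the allocation takes the scores.

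The MoCA, the Functional Independence Measure and the Clinical Frailty Score all pass through a rater's scoring. A rater who expects VR to help can mark one arm slightly higher, and a rater who doubts it can do the reverse. Such a shift enters when the score is written down, so no later step in the analysis can take it out. At stake is how far a long-term difference, or the lack of one, on these scores can be credited to VR.

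**Working it through.** **1. Does any section provide a masked 6-month rater?**

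| Question | Answer in the article | Place |
|---|---|---|
| Who interviews and tests at 6 months? | Study team; trained ICU nurses | {18a} |
| Is the research team blinded after allocation? | No, and no end point is given | {17a}, {16a} |
| Who is blinded? | The independent statistician | {17a}, {17b} |
| Which analyses are blinded? | Delirium incidence and duration only | {17a} |
| Who gives VR, and who enrols? | Study-team nurses; the study team | {11c}, {16c} |
| When does VR end? | ICU discharge, or day 14 at the latest | {18a} |
| Are the 6-month scores compared by arm? | Yes | {12} |

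No section provides one. {17b} limits its wording to the intervention period, but {17a} sets no end to the team's unblinding, so nothing restores masking for follow-up.

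**2. The plan's own figure.** The article gives no sizing, SD, follow-up rate or expected difference for any 6-month score. Its one sizing figure is 460 per group for delirium (39% against 30%, two-sided 0.05, 80% power). The standard two-proportion formula gives 437 per group without continuity correction and 459 with it, so 460 is reproduced with the correction. It serves here only as an upper limit on the number assessed per arm.

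**3. Illustration: how sensitive is the comparison to a rater shift?** These inputs are assumptions, not from the documents: no true effect, n assessed per arm, a common SD, and a uniform shift b between arms.

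- SE = SD × √(2/n)
- z = b / SE
- Chance of p < 0.05 (two-sided) = 1 − Φ(1.96 − z) + Φ(−1.96 − z)

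MoCA (30 points), n = 300, SD = 4: SE = 4 × √(2/300) = 0.327.

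- b = 0.5: z = 0.5/0.327 = 1.53, chance about 33%.
- b = 1.0: z = 1.0/0.327 = 3.06, chance about 86%.

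Range over n = 200 to 400 and SD = 4 to 5:

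| Shift | n = 200, SD 5 (SE 0.500) | n = 400, SD 4 (SE 0.283) |
|---|---|---|
| 0.5 point | 17% | 42% |
| 1.0 point | 52% | 94% |

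The same calculation in SD units, for any of the scores:

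| Shift | 460 per arm | 230 per arm (assumed 50% follow-up) |
|---|---|---|
| 0 | 5% | 5% |
| 0.1 SD | 33% | 19% |
| 0.2 SD | 86% | 57% |
| 0.3 SD | 99.5% | 90% |

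With samples of this size, a small systematic shift is enough to matter. The tables do not say how large the shift would be.

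**The case against.** **The outcomes rank low.** Outcomes {12} lists these scores after the primary and secondary outcomes, and Objectives {7} puts them among further objectives and speaks of describing differences. This stands and limits the weight. A reader might infer that the trial's main result is in doubt. The documents do not support that: the superiority claim does not rest on these scores, delirium incidence and duration are measured in the ICU, and survival comes from a central database.

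**The rater may not know the arm.** A reader might infer that the nurse at each visit does know it. The article does not say so. It only fails to require otherwise, and that the allocation is not needed at 6 months is an inference from there being no such task. The full protocol may also settle visit staffing. Even so, the article itself answers the question of who is blinded and names the assessors, and its answer leaves the 6-month rating open. An analysis plan could not repair this later.

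**The numbers are invented.** The n, SD and shift are assumed, and {18a} cites a reliability of 0.83 for the MoCA, a structured test. A reader might take 33% or 86% as the expected false-positive rate. They are not; they show sensitivity only.

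**Respondents know their arm too.** This stands. The EQ-5D-5L, and interview-based items on function and frailty, remain open to respondent expectation even with a masked rater. The gain from masking is therefore greatest for the MoCA, and it would go too far to blame any long-term difference wholly on the rater.

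**Conclusion.** The point holds for the rater-scored 6-month instruments: the MoCA chiefly, then the Functional Independence Measure and the Clinical Frailty Score. Followed as written, the article has an unblinded team rate outcomes that it then compares between arms, at a time when masking has become practical. The direction and size of any bias cannot be derived from the documents. Under the stated assumptions, a shift of 0.5 MoCA point raises the chance of a false significant difference from 5% to between 17% and 42%, and a shift of 1 point to between 52% and 94%. The change is worth making because it is cheap. The long-term claims are affected, not the delirium or survival results.

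**What to change.** In {17a} and {18a}:

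1. State that, where rostering allows, the 6-month assessment is done by an existing study-team nurse who neither enrolled that participant nor gave them VR, and whose REDCap role hides the allocation.
2. Have the assessor ask participants and relatives, at the start of the visit, not to mention the headset.
3. Record whether the arm became known, and report how often by arm.

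Do not exclude visits where the arm became known. Disclosure happens after randomisation and probably differs by arm, since only VR participants have a headset to mention, so dropping those visits would break the randomised comparison.

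**Cost.** An access setting, one tick box, rostering, and a record of who treated whom. Rostering may be tight: a participant can have up to 3 × 14 = 42 sessions, many nurses may have given at least one, and the team's size is not stated. Masking will be partial, because participants can reveal their arm and nurses on the same unit may learn it in other ways. Treatment, sample size and the primary analysis do not change.

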### Relevant concomitant care permitted or prohibited during the trial {11d}

All standard ICU care to treat the participant during their time in the ICU will be permitted.

### Provisions for post-trial care {30}

In the event of study-related damage or injuries, University Hospital Bern (Inselspital) shall provide compensation, except for claims that arise from misconduct or gross negligence of involved study personnel.

### Outcomes {12}

The primary outcome is delirium incidence, measured three times a day (morning, midday, and evening) by the Intensive Care Delirium Screening Checklist (ICDSC) as part of standard assessment. With the ICDSC, delirium is determined by consciousness, inattention, disorientation, hallucination, agitation or retardation, speech and mood, sleep/wake cycle disturbance, and fluctuation [19]. A unique incidence of delirium is counted once a patient reaches a score of ≥ 4, on a scale from 0 to 8 [20]. The entire period that a patient has a score ≥ 4 is considered as a single episode, and accordingly, counts only as a single incidence. The mean incidences of delirium per group will be looked at. The incidence of delirium is considered to be clinically relevant as it is known that patients who experience delirium while in critical care have worse long-term outcomes [4]. Furthermore, due to the possible influence of sedatives and analgesics on the incidence of delirium, both sedation and pain levels will be assessed every 2 h [5]. Consciousness and sedation will be measured using the Glasgow Coma Scale [21] and the Richmond Agitation Sedation Scale [22], respectively, and pain will be measured using the Numeric Rating Scale [23] and the Behavioural Pain Observation Tool [24].

As a secondary outcome, the duration of delirium will be evaluated per 8-h periods, or as needed, while patients are in the ICU. If the participant is assessed as delirious via the ICDSC during any of the assessments during an 8-h span, the entire period will count as delirious. Duration of delirium is clinically relevant knowing that the duration of delirium is an independent predictor of mortality 6 and 12 months post-ICU admission [25, 26].

Additional secondary outcomes include the pattern and intensity of movements, before and during delirium as well as between groups, measured continuously during the ICU stay. The fact that patients in delirium have fluctuating motor performance movement patterns, differing from baseline, could be a possible marker for delirium detection [27]. Therefore, acceleration will be measured with wearable sensors such as inertial measurement units, which have been previously used successfully in the ICU [28]. The monitoring of patients’ movement patterns could provide a means of early detection of delirium, permitting early intervention by the care staff.

Other pre-specified outcome variables include physiological parameters, feasibility of using the VR stimulation by ICU nurses, cognition at ICU discharge and 6 months post-discharge, health-related quality of life and functional independence before ICU admission and 6 months post-discharge, disease-related data, and survival 6 months post-discharge from the ICU. Physiological parameters (e.g. blood pressure, heart rate, respiration rate) will be recorded continuously and changes from baseline, or the start of an event such as VR stimulation, will be compared to later time points. The changes occurring in these parameters over time, together with disease-related data, are of interest and could indicate what effect, if any, VR stimulation has on the condition of the participant. Scores for health-related quality of life, functional independence, and clinical frailty before ICU admission and 6 months post-discharge, and cognition before ICU discharge and 6 months post-discharge, will be compared to determine if any significant differences occur. Additionally, the average survival 6 months post-ICU discharge will be compared between groups. Looking at these variables between groups is important as cognition, health-related quality of life, independence, frailty, and mortality, among others, are known to be negatively impacted by the presence of delirium during the time spent in the ICU. Therefore, it is meaningful to identify if there were any significant changes in these aspects for individuals in the treatment group compared to the controls. It will also be important to determine if providing such an intervention is feasible for the care providers. For this, the validated System Usability Scale will be completed by the nurses in order to understand if overall, the use of this technology was accepted and whether or not it could be integrated into standard ICU care practices [29].

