## Data collection and management

### Plans for assessment and collection of outcomes {18a}

The study starts within 24 h after admission to the ICU. In the enrolment phase, participants will be randomly assigned to either the intervention or the control group, with the intervention beginning as soon as possible following enrolment. Three times a day (between 7:00 am and 7:00 pm) for 30 min, participants in the intervention group will receive the intervention (VR stimulation) applied directly in the bed. The intervention will be included in the daily schedule of the patients. The intervention period ends when the patient is discharged from the ICU or at the latest 14 days after admission to the ICU. Thus, the intervention period depends on the length of stay in the ICU and can vary between participants.

After allocation, incidence and duration of delirium is assessed in three shifts a day. If delirium is diagnosed, the standard ICU delirium therapy (local delirium protocol) will be started, regardless of the participants’ group. VR stimulation will optimally start before this time point. Delirium is assessed using the ICDSC which is a reliable (Cohen’s kappa (*κ*) = 0.60) [33] and specific (95%) [33] tool to detect delirium in ICU patients [5] and was translated into German by Radtke et al. [34]

Assessment of sedation will be done using the Richmond Agitation Sedation Scale which has a reliability of *κ* = 0.91 and a face validity with 81–92% agreement [22, 35]. Consciousness will be evaluated according to the Glasgow Coma Score which was originally found to have a *κ* = 0.66–0.77 for the whole scale, but has since been found to have higher reliability when looking at the eye, motor, and verbal scales individually (*κ* = 0.89, 0.94, and 0.88, respectively) [21, 36]. The validity for the Glasgow Coma Scale, however, remains controversial with some stating that the validity has been well established [37], while others question how the scale is assessed under different conditions such as sedation or intubation [36]. Pain will be assessed using the Numeric Rating Scale with an interrater reliability score of *κ* = 0.71 [23] and the Behavioural Pain Observation Tool which has a *κ* = 0.80 and a content validity index of 0.73–1.0 [24].

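### The protocol article gives inconsistent ICDSC scoring times and does not exclude unscheduled scores, so the chance of being found delirious can differ between unblinded arms

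*Protocol article*

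**What the plan says.** The protocol article describes the timing of delirium scoring in three ways.

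- Primary outcome, Outcomes {12}: "measured three times a day (morning, midday, and evening) by the Intensive Care Delirium Screening Checklist (ICDSC", which the section describes as standard assessment.
- Duration, same section: "the duration of delirium will be evaluated per 8-h periods, or as needed, while patients are in the ICU".
- Both outcomes, Plans for assessment and collection of outcomes {18a}: "After allocation, incidence and duration of delirium is assessed in three shifts a day".

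Two counting rules in Outcomes {12} act on these scores. For incidence: "A unique incidence of delirium is counted once a patient reaches a score of ≥ 4, on a scale from 0 to 8". For duration, a positive ICDSC "during any of the assessments during an 8-h span, the entire period will count as delirious".

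On blinding, Who will be blinded {17a} states: "The research team will not be blinded after assignment to interventions". It adds that the interprofessional team is not blinded when carrying out the intervention. The analysis of incidence and duration is to be blinded. Blinded scoring of the ICDSC is not provided for anywhere.

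**The concern.** Incidence and duration both depend on how often, and when, a patient is scored. Three 8-h periods or shifts cover the whole day; morning, midday and evening name no night assessment. If a site follows the narrower wording, one period in three has no scheduled score, although duration is counted in those periods.

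The second problem is discretionary scoring. Duration may be evaluated as needed, and one positive result turns the full 8 h delirious. More scores in a period therefore mean more chances of a positive. Nothing restricts the incidence rule to scheduled scores, and {18a} treats incidence and duration as assessed together, so an unscheduled positive could also create a primary event.

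Staff who know the allocation decide when an extra check is made. The Introduction says that delirium most often presents with hypoactivity and evades diagnosis, and is easier to recognise in agitated patients, so checks made on suspicion are likely to favour agitated cases. At stake is an arm difference that reflects how often patients were looked at.

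**Working it through.** **Side-by-side reading**

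| Place | Outcome covered | Routine scores per day | Night covered? | Unscheduled scores |
|---|---|---|---|---|
| Outcomes {12}, primary | Incidence | 3 | Not named | Not mentioned |
| Outcomes {12}, secondary | Duration | 3 (8-h periods) | Yes, if every period is scored | Allowed |
| Plans for assessment {18a} | Both | 3 (shifts) | Yes, if the shifts span 24 h | Not mentioned |

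The number of routine scores agrees. Night coverage and the status of unscheduled scores do not. On the narrow reading, a patient who stays the full 14 days has 14 × 3 = 42 periods, of which 14 × 1 = 14 have no scheduled score. Shorter stays have proportionally fewer.

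**The plan's own figure**

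Inputs from Sample size {14}: 39% against 30%, two-sided 0.05, 80% power, 460 per group.

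Uncorrected n per arm = [1.96·√(2·0.345·0.655) + 0.8416·√(0.39·0.61 + 0.30·0.70)]² / 0.09² = 437. With the continuity correction it is 459 per arm, or 918 in total, which reproduces the stated 920. Power at 460 per arm is 0.820 uncorrected and 0.801 corrected. The scoring issue does not alter this calculation. It affects whether the observed proportions mean the same thing in both arms.

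**Illustration 1: extra events in one arm, no true effect**

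Assume a common detected rate p in both arms and e further percentage points detected in one arm only. With n = 460, let p̄ be the mean of the two rates, and set:

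- se0 = √(2·p̄(1−p̄)/n)
- se1 = √([(p+e)(1−p−e) + p(1−p)]/n)
- rejection probability = 1 − Φ((1.96·se0 − e)/se1) + Φ((−1.96·se0 − e)/se1)

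For p = 0.30 and e = 0.02, se0 = 0.03050 and se1 = 0.03049. The result is 1 − Φ(1.304) + Φ(−2.616) = 0.096 + 0.004 = 0.10.

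| Extra events in one arm | p = 0.30 | p = 0.39 |
|---|---|---|
| 1 point | 0.063 | 0.061 |
| 2 points | 0.101 | 0.095 |
| 3 points | 0.165 | 0.153 |
| 5 points | 0.367 | 0.337 |

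The figures are the same whichever arm has the extra events; only the favoured arm changes.

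**Illustration 2: cases missed equally in both arms**

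If unscored nights lost 10% of cases in each arm, the rates would be 35.1% and 27.0% and power would fall from 0.82 to 0.76. A loss of 20% (31.2% and 24.0%) would bring it to 0.69. Both are uncorrected, at 460 per arm.

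The extra and missed shares are assumptions. The documents give no value for either.

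**The case against.** The case on the other side is substantial.

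- All the texts agree on three routine scores a day, and the three times of day may be loose labels for three shifts. The schedule figure is not shown and the article is condensed, so exact times may stand elsewhere. This holds: a night gap follows only from the narrow reading.
- The as-needed wording is attached to duration, the secondary outcome. This also holds: its effect on incidence is an inference from an incidence rule that does not exclude such scores.
- Sedation and pain are assessed every 2 h, with no restriction to one arm, so the VR contacts add less observation than one might think. The Discussion plans a cross-check of the ICDSC against the Richmond scale. Both soften the concern. Neither fixes which ICDSC scores count, and a positive Richmond score points to agitation and would not pick up hypoactive cases.
- The fluctuation and sleep/wake items describe change over time, so a morning score can partly reflect the night. That reduces the loss from an unscored night but does not remove it.
- The analysis is blinded. That protects the analysis and leaves the scoring exposed.

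Two stronger readings are tempting. A reader might infer that ICDSC scores coincide with VR sessions, because both use the same times of day. No ICDSC clock times are given, and the window from 7:00 am to 7:00 pm belongs to the sessions only.

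A reader might also take the 95% specificity in {18a}, assume independent scores over a 4-day stay, and compare 1 − 0.95^12 = 0.46 with 1 − 0.95^16 = 0.56 for one extra score a day in one arm. The 10-point gap then seems to exceed the 9-point effect (39% against 30%). It applies only to delirium-free patients, however. Over a whole arm it is 0.10 × 0.61 = 6.1 or 0.10 × 0.70 = 7.0 points, below 9. Independence is also unrealistic: it would put measured control incidence at 0.39 + 0.61 × 0.46 = 67%.

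**Conclusion.** The concern holds in a limited form. The scoring statements in Outcomes {12} and {18a} differ on night coverage. The any-positive rule lets discretionary scores by unblinded staff set duration, and nothing keeps those scores out of incidence. This goes beyond condensed detail, because the counting rules as stated make the result depend on the number of scores taken.

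The direction of bias cannot be told in advance. More contact with VR patients could add events in that arm, while staff expectations could add them among controls. The size is unknown from the documents. The rise in type I error to about 0.10 to 0.16 rests on an assumed 2 to 3 points of extra events in one arm, 460 patients per arm and no true effect. It shows that a small imbalance would matter, and it does not predict that one will occur. The documents do not support saying that nights are certainly unscored, that scoring falls at VR sessions, or that the bias would exceed the planned effect.

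**What to change.** Reconcile Outcomes {12} and Plans for assessment {18a} to one rule: one scheduled ICDSC in each 8-h shift, night included, identical in both arms. Derive primary incidence and duration from these scheduled scores only. Continue to record as-needed scores, marked as unscheduled, and add a pre-specified sensitivity analysis that includes them. Reporting the number of unscheduled scores by arm would show whether ascertainment was balanced.

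The cost should be mainly wording, since the article calls the ICDSC part of standard assessment and already refers to three shifts. If night scoring is not routine at the site, it adds one score per patient per day. The statistical downside is that an episode seen only on an unscheduled check may be missed in the main analysis; the sensitivity analysis would show how often that happens.
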